# The effect of oligofructose-enriched inulin supplementation on gut microbiota, nutritional status and gastrointestinal symptoms in paediatric coeliac disease patients on a gluten-free diet: study protocol for a pilot randomized controlled trial

**DOI:** 10.1186/s12937-017-0268-z

**Published:** 2017-08-22

**Keywords:** Coeliac disease, Prebiotic, Oligofructose-enriched inulin, Gluten-free diet, Supplementation, Gut microbiota

## Abstract

**Background:**

A lifelong gluten-free diet (GFD) is regarded as the only proven and accepted therapy for coeliac disease (CD). However, even patients who strictly follow a GFD often suffer from intestinal symptoms and malabsorption. Selective modulation of intestinal microbiota with prebiotics could remedy various symptoms associated with CD. The use of prebiotics in the treatment of intestinal diseases remains insufficiently investigated. To our knowledge, this study makes the first attempt to evaluate the effect of prebiotic supplementation on gastrointestinal symptoms and nutritional status of children with CD. We hypothesized that adherence to a GFD supplemented with oligofructose-enriched inulin (Synergy 1) would deliver health benefits to children suffering from CD without any side effects, and that it would alleviate intestinal inflammation, restore and stabilize gut microbial balance and reverse nutritional deficiencies through enhanced absorption of vitamins and minerals.

**Methods:**

A randomized, placebo-controlled clinical trial was designed to assess the impact of the Synergy 1 on paediatric CD patients following a GFD. We randomized 34 children diagnosed with CD into an intervention group receiving 10 g of the Synergy 1 supplement daily and a placebo group (receiving maltodextrin) during a 12-week nutritional intervention. Selected biochemical parameters, nutritional status and the characteristics of faecal bacteria will be determined in samples collected before and after the intervention. Analysis of vitamins and amino acids concentration in biological fluids will allow to assess the dietary intake of crucial nutrients. The compliance to a GFD will be confirmed by a Food Frequency Questionnaire (FFQ-6) and the analysis of serum anti-tissue transglutaminase and faecal gluten immunogenic peptides (GIP).

**Conclusion:**

The identification of the beneficial effects of the Synergy 1 supplement on children with CD could have important implications for nutritional recommendations for CD patients and for alleviating the harmful effects of the disease.

**Trial registration:**

ClinicalTrials.gov Registration Number: NCT03064997.

**Electronic supplementary material:**

The online version of this article (doi:10.1186/s12937-017-0268-z) contains supplementary material, which is available to authorized users.

## Background

Coeliac disease (CD) is a chronic inflammation of the intestinal mucosa resulting from an excessive immune response to a dietary gluten (mixture of proteins found in wheat, rye and barley) in genetically predisposed individuals, both children and adults [1]. The disease is relatively prevalent, and it affects approximately 1% of the general population, although the majority of cases remain undiagnosed [1]. In addition to the inflammation of the small intestine, CD can also be manifested by other symptoms affecting different organs or tissues [2, 3]. The classical form of the disease involving intestinal symptoms and malabsorption (diarrhoea, vomiting, abdominal pain) is more frequently diagnosed in children than adults. Unapparent manifestations of the disorder involving non-intestinal clinical symptoms such as anaemia, decreased bone mineral density and mental abnormalities are more common in older patients. Untreated CD could lead to chronic inflammation, malabsorption and nutritional deficiencies. A strict, lifelong gluten-free diet (GFD) which requires complete abstinence from foods and grains that contain gluten (wheat, rye, barley) is regarded as the only proven and accepted therapy for CD. Research indicates that rigorous observance of GFD alleviates gastrointestinal symptoms [4] and restores gut health in CD patients [5], however, compliance with GFD guidelines varies considerably from 80% to less than 40% [6]. Many CD patients who observe a strict GFD continue to experience symptoms of the disease. In 20–80% of patients following a GFD, the mucosal lesions (Marsh II and III) were reported [7] similar to intestinal epithelia impairment that is noted in newly diagnosed patients. In microbiological studies [8–10], the diversity of *Lactobacillus* and *Bifidobacterium* bacteria was reduced in CD patients, which is associated with intestinal dysbiosis. According to Wacklin et al. [11], intestinal dysbiosis is linked with persistent gastrointestinal symptoms in CD patients on a GFD. Iron deficiency and anaemia are also common complications in CD, and their prevalence ranges from 12% to 69% of newly diagnosed patients [12]. Lower bone mass density was determined in 74% of adult CD sufferers who stuck to a GFD for long periods of time [10]. Taking into consideration the abovementioned research results, it could be suggest that GFD alone may not effectively reverse the clinical symptoms and re-establish intestinal microbiota balance in CD patients, even if GFD is still considered the most rational treatment approach. For this reason, several new therapies have been proposed as an alternative to a GFD [13] however, studies assessing the efficacy of the new treatments are expensive and are still at the research stage. Meanwhile, prebiotics as naturally-occurred plant-derived compounds seem to be promising and safe additive to a GFD demonstrating the beneficial influence on human health.

Prebiotics selectively stimulate the growth and activity of potentially health-promoting strains of bacteria in the intestine, mainly *Bifidobacterium* and *Lactobacillus*. Many studies report positive prebiotic-induced changes in the microbial composition alongside the beneficial health effects however, only few studies investigated the impact of prebiotics on patients with intestinal inflammation. Research investigating the effectiveness of prebiotics in managing chronic intestinal diseases is still in its infancy, but prebiotics’ ability to regulate the activity of gut microbiota could be harnessed to remedy various symptoms associated with CD. Data from the in vitro studies and the animal model studies, yet promising but do not allow to formulate a final conclusion about the effects of prebiotics therefore, the evidence for such beneficial effects in human subjects is urgently needed. Only few pilot human studies concerning the impact of prebiotics on intestinal inflammation is available [14, 15]. Besides the fact that a limited number of such human studies have been performed, most of them have limitations as they investigated prebiotic effects in combination with the administration of other ingredients or did not include an appropriate control group. To fill this research gap, a randomized, placebo-controlled clinical trial was designed to assess the influence of the oligofructose-enriched inulin on paediatric CD patients following a GFD.

Based on the literature data, it could be hypothesized that the inclusion of prebiotics in GFD could be an easy to administer and cost-effective alternative treatment for CD. Balanced gut microbiota is a crucial determinant of health, and further research is needed to evaluate the safety and efficacy of prebiotic supplements for CD patients. By presenting this research protocol we are counting on a productive discussion concerning a GFD and the possible dietary methods of its modulation aimed to increase the effectiveness of GFD in CD. The initiated dialog between researchers of various field of interest, including food scientists, dieticians, and gastroenterologists might give the rationale for the further interdisciplinary research, concerning the modulation of gut microbiota and the intestinal functionality induced by nutrients and functional dietary ingredients, in the wide context of the novel dietary strategies in health and disease. The establishment of the cooperation with other research centres may possibly result in the extensive multi-centre research concerning this interesting but scantly investigated subject.

### Research objective and hypothesis

We hypothesized that adherence to a GFD supplemented with oligofructose-enriched inulin would deliver health benefits to children suffering from CD without any side effects, and that it would alleviate intestinal inflammation, restore and stabilize balance of a gut microbiota and reverse nutritional deficiencies through enhanced absorption of vitamins and minerals. The main aim of this clinical trial is to evaluate the impact of an oligofructose-enriched inulin (Synergy 1) on selected biochemical parameters and nutritional status of paediatric CD patients following a GFD. Attempts are also being made to determine the influence of the oligofructose-enriched inulin supplement on the quantitative composition and the activity of intestinal microbiota.

## Study design

This pilot, single-centre, randomized, parallel-group, placebo controlled nutritional intervention was conducted over a period of 12 weeks to determine the impact of oligofructose-enriched inulin on biochemical parameters, nutritional status and gut microbiota characteristics of paediatric CD patients who followed a GFD. The schedule of the enrolment, interventions, and assessments according to SPIRIT requirements is shown in Fig. 1. The clinical study design is presented in Fig. 2. This study is reported according to the Strengthening the Reporting of Observational Studies in Nutritional Epidemiology (STROBE-nut) checklist [16].

**Fig. 1 Fig1:**
[figure not shown]
Content for the schedule of enrolment, interventions, and assessments according to SPIRIT requirements

**Fig. 2 Fig2:**
[figure not shown]
Flow diagram of participant recruitment during the trial according to CONSORT

### Participant selection

Children and adolescents (aged 4 to 18 years) diagnosed with CD based on the criteria developed by the European Society for Paediatric Gastroenterology, Hepatology and Nutrition (ESPGHAN) [17] were recruited from among the patients of the Department of Paediatrics, Gastroenterology and Nutrition of the Children’s Hospital in Olsztyn at least 6 months before the study. Detailed inclusion and exclusion criteria are presented in Table 1. Around 150 children receive treatment for CD at the Department of Paediatrics, Gastroenterology and Nutrition of the Children’s Hospital in Olsztyn. The participants were recruited for the study between November 2015 and January 2016. A total of 96 CD patients were invited to participate in the pilot trial during regular visits at the clinic or by way of an invitation letter describing the details of the planned trial. Ultimately, 34 subjects who met the inclusion criteria (outlined in Table 1) and whose parents/legal guardians signed voluntary consent forms were enrolled in the study. The trial started in winter months, and all subjects were advised to continue their long-term vitamin D supplementation.

**Table 1 Tab1:** Participant eligibility criteria

Inclusion criteria:
Coeliac disease confirmed by serological, genetic and biopsy analyses
Gluten-free diet for at least 6 months
Younger than 18
Patient of the Gastroenterology Clinic at the Regional Specialist Children’s Hospital in Olsztyn, Poland
Parents or caregivers are willing to give written informed consent for the child’s participation in the trial
Exclusion criteria:
Antibiotics in the month preceding the study
Medication for osteoporosis (bisphosphonates, calcium calcitonin), probiotics, prebiotics or fibre supplements
Poor or average overall health
Current enrolment in another research study
Recent surgery

### Ethical aspects

Parents and caregivers were informed about the potential benefits and risks of the dietary intervention, and they signed an informed consent form during the enrolment visit. The experimental design and procedures were approved by the Bioethics Committee of the Faculty of Medical Sciences of the University of Warmia and Mazury in Olsztyn (agreement No: 23/2015 of 16 June 2015). The study was registered at http://www.clinicaltrials.gov (registration number NCT03064997).

### Randomization and blinding

Patients have been randomly assigned to an intervention group (*n* = 18) or a placebo group (*n* = 16). Stratified randomization based on gender and age was conducted by a researcher not directly involved in the study. Separate randomization procedures were carried out for boys and for girls to produce comparable groups. The trial had a design where the researchers, laboratory personnel (excluding the researcher who distributed the supplement or the placebo to the participants) and the participants were not aware which subjects were receiving the supplement and which were receiving the placebo.

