### Sample size

To our knowledge, this study makes the first attempt to evaluate the effects of fructan supplementation on children with CD, therefore, it was performed as a pilot trial without calculating sample size. Our plan was to recruit approximately 30 children (15 subjects per arm) with diagnosed CD on the assumption that the drop-out rate would reach approximately 20% (12 participants in each arm would complete the trial). The results obtained in the pilot study will be used to calculate the sample size for a fully-powered study that will be carried out in the future on paediatric CD patients receiving oligofructose-enriched inulin with GFD.

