### Statistical analysis

Anthropometric and demographic data will be analysed using descriptive statistical methods. The participants whose reported intake of the Synergy 1 supplement or the placebo exceeded 80% of the prescribed intake will be included in final analyses. Statistical analyses will be performed in duplicate and expressed as mean values and standard deviation (SD). The influence of prebiotic supplemented-GFD and placebo supplemented –GFD on the measured parameters will be determined by one-way analysis of variance (ANOVA). If the differences between experimental and placebo groups are statistically significant (*P* < 0.05), the data will be subjected to post-hoc comparisons with the use of Fisher’s Least Significant Difference (LSD) test. The side effects of supplementation will be expressed by the percentage of each effect noted in the experimental group or the placebo group. The average consumption of food products by CD children during the intervention trial obtained from FFQ-6 will be compared in the Kruskal-Wallis test. Data will be processed statistically using Statistica 12 software (StatSoft, USA).

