Despite the beneficial effects of prebiotics on animals, their usefulness in the treatment of inflammatory bowel disease in humans has been investigated by very few studies. Welters et al. [27] conducted a randomized, double-blind crossover study of patients with stable asymptomatic pouchitis whose diets were supplemented with inulin. The cited authors reported a decrease in pouchitis disease activity index (PDAI) scores as well as a decrease in gut pH, faecal *Bacteroides fragilis* counts and the content of secondary bile acids. In a different study, the administration of the Synergy 1 in combination with the *Bifidobacterium longum* probiotic to patients with ulcerative colitis significantly increased the counts of Bifidobacteria colonizing rectal mucosa [14]. The above was accompanied by a highly significant decrease in the levels of mucosal proinflammatory cytokines (TNF-α, IL-1a) and inducible β-defensins 2, 3 and 4 which are important markers of epithelial healing. Smecuol et al. [15] recently found that inulin-type fructans (ITF) contribute to the proliferation of *Bifidobacterium infantis* probiotic strains which have a confirmed beneficial effect on patients with active CD.

The described trial had certain limitations. Above all, sample size was not determined due to the absence of primary outcome data. However, the presented results can be used for retrospective calculations and to estimate the power of a full-size trial in the future. Another limitation is related to the participants’ characteristics, in particular the wide age span and differences in GFD duration. However, a protocol for reporting any effects observed in the group of available subjects was developed during this pilot trial. In a follow-up, full-size, multicentre study, a larger population will be investigated and differentiated according to age, duration of GFD and/or other parameters.

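### Randomisation is stratified on gender and age, but the one-way ANOVA includes neither, so precision is lost for laboratory and faecal outcomes that vary with age or sex

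*Protocol article*

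**What the plan says.** On allocation, the Protocol article (Randomization and blinding) says "Stratified randomization based on gender and age was conducted by a researcher not directly involved in the study" and adds "Separate randomization procedures were carried out for boys and for girls to produce comparable groups". How age was stratified, for instance by which bands, is not described. The result was 34 children: "Patients have been randomly assigned to an intervention group (*n* = 18) or a placebo group (*n* = 16").

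On analysis (Statistical analysis), the effect of the two diets "on the measured parameters will be determined by one-way analysis of variance (ANOVA"), with a 0.05 threshold and Fisher's LSD afterwards. No covariate or stratum term is named anywhere in the article. The same section gives anthropometric and demographic data descriptive statistics only, compares FFQ-6 consumption by Kruskal-Wallis, and reports side effects as percentages.

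The Discussion names as a limitation the participants' characteristics, "in particular the wide age span and differences in GFD duration", and leaves differentiation by age to a later, larger study. Under Sample size, the results are to be used to size that study.

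**The concern.** Stratifying on a prognostic factor reduces the chance variation of the group difference. The benefit shows in the standard error only if the analysis also contains the factor. A one-way ANOVA leaves the sex and age variation in its residual mean square, so the test does not use precision that the design has already secured.

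Ages run from 4 to 17 years (Table 2), and some tested measures, such as serum and urine creatinine and phosphorus, can be expected to change over that range. Two things are at stake: power within this small trial, and the SD that the pilot passes on. If the full trial is analysed with age and sex in the model but sized from an SD that still contains their variation, its sample size will be too large.

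**Working it through.** **Inputs from the article.** Arms of 18 and 16. Girls 11/18 = 61.1% and 10/16 = 62.5% (Table 2). Mean age 10 in both arms, range 4 to 17 overall (Table 2). Threshold 0.05; with two groups the ANOVA F test equals a two-sided t test. No SD, effect size or power is given: "it was performed as a pilot trial without calculating sample size".

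**Input not in the documents.** R², the share of outcome variance explained by sex and age. It is assumed and varied below.

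**Step 1. The plan's own figure.** The only sample-size arithmetic is the completer count: 15 × (1 − 0.20) = 12 per arm, and 24 / (1 − 0.20) = 30 in total. It reproduces. There is no power statement to check.

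**Step 2. Upper limit by formula.** With perfect balance on both factors, the variance of the group difference is σ²(1 − R²)(1/n₁ + 1/n₂), while one-way ANOVA estimates σ²(1/n₁ + 1/n₂). The ratio of reported to true standard error is 1/√(1 − R²):
- R² = 0.1: 1/√0.9 = 1.054
- R² = 0.2: 1/√0.8 = 1.118
- R² = 0.3: 1/√0.7 = 1.195

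**Step 3. Simulation with realistic balance.** 6,000 trials per scenario. There were 34 children, about 62% girls, with ages uniform from 4 to 18. They were allocated in pairs within sex, ordered by age, so the arms differ by at most two children. R² was split 80% age and 20% sex (assumption). The effect was set for about 80% power in the adjusted model at 18 v 16. "SE ratio" is the mean ANOVA standard error divided by the actual SD of the estimated difference.

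| R² | SE ratio, ANOVA | Type I error, ANOVA | Type I error, adjusted | Power, ANOVA | Power, adjusted |
|---|---|---|---|---|---|
| 0 | 1.00 | 5.2% | 4.9% | 80.8% | 80.5% |
| 0.1 | 1.04 | 3.9% | 4.9% | 77.4% | 80.6% |
| 0.2 | 1.09 | 3.5% | 5.2% | 73.1% | 80.2% |
| 0.3 | 1.15 | 2.6% | 5.1% | 66.7% | 78.8% |

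The power differences are 80.6 − 77.4 = 3.2, 80.2 − 73.1 = 7.1 and 78.8 − 66.7 = 12.1 points. At the 24 planned completers (12 per arm), ANOVA power is 76.0%, 72.5% and 65.8%, against 78.6%, 79.5% and 79.1% adjusted. At R² = 0 the adjusted model there has 79.4% against 80.2%, a cost of 0.8 points.

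**Step 4. If age was not balanced by design.** Only the sex mechanism is described. With R² = 0.3 and the 80/20 split, sex alone explains 0.2 × 0.3 = 0.06. The SE ratio is then about 1/√0.94 = 1.03, and the type I error about 2 × [1 − Φ(1.96 × 1.03)] ≈ 4.3%. The test is then hardly conservative, but age variation still sits in the error term and still costs power.

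**Step 5. The SD passed on.** An unadjusted residual variance exceeds the adjusted one by 1/(1 − R²): 1/0.9 = 1.11, 1/0.8 = 1.25 and 1/0.7 = 1.43. A later trial that adjusts for sex and age but is sized from the unadjusted SD would be about 11%, 25% or 43% too large.

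**The case against.** The strongest case is that the consequence is small and uncertain.

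- **Error in the safe direction, in a pilot without a power claim.** True. Nothing is biased, false positives are not inflated, and no stated power figure is contradicted.
- **R² is unknown.** True. If sex and age do not predict an outcome, nothing is lost. The figures are a range under assumption.
- **Most tested outcomes have a T0 value.** Blood, urine and faecal measures are taken at T0 and T1, and T0 may absorb much of the stable age and sex variation. What sex and age add beyond T0 is then smaller than the table shows. The article does not state T0 adjustment, however, nor whether the ANOVA is run on T1 values or on changes.
- **The most age-dependent measures are not tested by ANOVA.** True. Weight, height and BMI are only described, and BMI is also expressed as SDS for age and sex. FFQ-6 goes to Kruskal-Wallis, to which the figures above do not carry over directly. The point therefore rests on the laboratory and faecal measures.
- **The analysis plan is not shown.** This does not answer the point, because the article itself names the model and the post-hoc test. If the post-hoc test means that group-by-visit cells were intended, sex and age are still absent.

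None of this removes the mismatch between allocation and analysis, and none shows a material cost of correcting it.

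**Conclusion.** The trial is randomised by gender and age and analysed without them. For ANOVA-tested laboratory and faecal outcomes that vary with age or sex, this loses precision and power and inflates the residual SD meant for planning. With good balance on both factors and assumed R² of 0.1, 0.2 and 0.3, the standard error is about 4%, 9% and 15% too large and about 3, 7 and 12 points of power are lost. The loss is nil at R² = 0, and the gain is smaller where T0 already carries the age and sex information.

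Three stronger readings are not supported:
- A reader might infer that the group comparison is biased or prone to false positives. Leaving out balanced prognostic factors does neither; the type I error falls below 5%.
- A reader might take the Step 2 ratios (12% and 20% at R² of 0.2 and 0.3) as the size of the error. They need perfect balance on both factors. The article describes a mechanism only for sex, and equal mean ages in Table 2 do not show how closely age was matched.
- A reader might extend the point to weight, height, BMI or food scores. The article does not assign these to the ANOVA.

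This is an efficiency and planning weakness, not a threat to validity.

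**What to change.** For tested outcomes measured at T0 and T1, replace the one-way ANOVA with a linear model: T1 on group, T0, sex and age (years, continuous). For any tested outcome measured only at the end of the study, use outcome on group, sex and age, in an ordinal or rank-based form for scores. Report the residual SD from these models, since that is the figure an age- and sex-adjusted full trial needs. Leave the descriptive summaries and side-effect percentages as they are.

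The cost is a change of wording and two degrees of freedom for sex and age. If neither is prognostic, at most about 1 point of power is lost, even with 12 children per arm. Both variables are already recorded for every child, and the article describes many of the assays as still to be done.
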